***Long-term outcomes***
▪ **Recurrent stroke** (if with record frequency, interval, and etiology)
▪ **Unfavorable functional outcome at follow-up**^b^
▪ Mortality
▪ Stroke during subsequent pregnancy
• **Offspring**
***Short-term outcomes***
▪ **Neonatal asphyxia** (assessed by Apgar scores)^c^
▪ Intrauterine death or stillbirth
***Long-term outcomes***
▪ **Developmental status** (assessed by ASQ-3) **at follow-up**^d^
▪ Critical illness (if with record etiology)^e^

*mRS* modified Rankin Scale, *EQ-5D* EuroQol five dimensions questionnaire *ASQ-3* Ages & Stages Questionnaires, Third Edition

^a^Short-term outcomes are defined as events occurring during hospitalization, while long-term outcomes are defined as health status within 1-year post-discharge and during follow-up. All participants will be followed up through telephone interviews. The initial follow-up is scheduled to take place between December 2024 and February 2025. The follow-up phase will consist of three rounds, each lasting 3 months and conducted every 3 years

^b^Functional outcomes will be assessed using the modified Rankin Scale (mRS), with an mRS score greater than 2 defined as an adverse outcome

^c^Neonatal asphyxia will be assessed using Apgar scores at 1, 5, and 10 min, with scores of 8–10 defined as no asphyxia, 4–7 as mild asphyxia, and 0–3 as severe asphyxia

^d^The ASQ-3 categorizes developmental status into five subdomains: (1) Communication, (2) gross motor, (3) fine motor, (4) problem-solving, and (5) personal-social. Based on scores in each subdomain, results will be classified as “above,” “close to,” or “below” the threshold

^e^Critical illness is defined as the offspring requiring hospitalization due to a diagnosed disease, including neurological diseases, cardiovascular diseases, gastrointestinal diseases, respiratory diseases, urological diseases, hematological and immunological diseases, and other major disorders

Functional outcomes will be assessed using the modified Rankin Scale (mRS), with an mRS score greater than 2 defined as an adverse outcome. An independent assessment team, composed of professionals who did not participate in the patients’ treatment, will be responsible for evaluating functional outcomes during follow-up to ensure objectivity and reduce potential bias. Members of this assessment team will receive systematic training to ensure their proficiency in the assessment criteria and procedures of the mRS and EQ-5D questionnaires, thereby enhancing the reliability of the assessment results.

Specific assessment criteria include the following:

The assessor will conduct the mRS scoring for each patient during the follow-up period through standardized interviews and questionnaires combined with clinical observations. The assessor will use a unified mRS scoring guideline to ensure the consistency of scoring. The assessor will supervise and guide patients to take the test using the validated Chinese version of the EQ-5D5D questionnaire.

##### Assessment process

Assessors will document changes in patients’ functional status during follow-up, including self-reported and observed capabilities in activities of daily living, to accurately evaluate functional outcomes.

Neonatal asphyxia will be assessed using Apgar scores at 1, 5, and 10 min, with scores of 8–10 defined as no asphyxia, 4–7 as mild asphyxia, and 0–3 as severe asphyxia. The assessment will be conducted by healthcare personnel trained specifically in neonatal care to ensure the accuracy and consistency of the scores.

Developmental outcomes for offspring will be assessed using the Ages and Stages Questionnaire, Third Edition (ASQ-3), which is one of the most widely used tools for screening comprehensive developmental status in children aged 1 to 66 months. The ASQ-3 categorizes developmental status into five subdomains: (1) Communication, (2) gross motor, (3) fine motor, (4) problem-solving, and (5) personal-social. Based on scores in each subdomain, results will be classified as “above,” “close to,” or “below” the threshold. The assessment will be conducted by trained assessors to ensure the reliability and accuracy of the results [14].

Recurrent stroke and stroke during subsequent pregnancy are defined as events where women experience a recurrent stroke and a stroke during a subsequent pregnancy, respectively, both confirmed by corresponding medical or insurance records. Intrauterine death or stillbirth is defined as a dead fetus in the uterus at any trimester or the birth of a dead infant after 28 + 1 weeks of gestation. Critical illness is defined as the offspring requiring hospitalization due to a diagnosed disease, including neurological diseases (such as epilepsy and cerebral palsy), cardiovascular diseases (such as congenital heart disease), gastrointestinal diseases (such as necrotizing enterocolitis), respiratory diseases (such as allergic asthma), urological diseases (such as hypospadias), hematological and immunological diseases, and other major disorders.

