**Fig. 1 Fig1:**
[figure not shown]
The geographical distribution of centers participating in the ASPP study. The ASPP study aims to include 36 territorial or regional centers across 22 provinces in China

ASPP patients and non-ASPP participants from January 2015 to November 2024 will be included (Fig. 2). Table 1 lists the inclusion criteria and exclusion criteria. ASPP patients are defined as those who experience acute stroke events during pregnancy or within 6 weeks postpartum, confirmed by neuroimaging evidence of cerebral infarction or hemorrhage corresponding to their symptoms.

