### Follow-up schedule

All participants will be followed up through telephone interviews. The initial follow-up is scheduled to take place between December 2024 and February 2025. The follow-up phase will consist of three rounds, each lasting 3 months and conducted every 3 years. The specific follow-up schedule is as follows:(1) First follow-up: Conducted between December 2024 and February 2025, focusing on stroke recurrence, cardiovascular health indicators, and quality-of-life assessments. During this period, any newly occurring stroke events will be documented, including the nature and severity of recurrent strokes, and changes in cardiovascular risk factors, such as blood pressure and lipid levels, will be monitored.(2) Second follow-up: Conducted between December 2027 and February 2028, continuing with telephone interviews and standardized questionnaires to assess participants’ life quality, including emotional state and daily activity capacity, while monitoring stroke and cardiovascular health status(3) Third follow-up: Conducted between December 2030 and February 2031 to further observe late-stage stroke and cardiovascular disease, particularly focusing on the increased cardiovascular risk phase post-menopause.

If participants report a stroke recurrence during the follow-up period, researchers will obtain the hospitalization records through the following process to confirm the event: First, researchers will contact the participant’s attending physician or the relevant hospital to systematically request the hospitalization records and medical information. Second, relevant medical records will be reviewed to verify the reported recurrence event, including confirmation of diagnosis, treatment course, and length of hospitalization. Additionally, if necessary, researchers will request neuroimaging assessments (such as CT or MRI) to further confirm the nature and severity of the stroke.

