#### Primary outcome

These are the following: For Aim 1, composite unfavorable outcome defined as *mRS* > 2 or EQ-5D index score < 0.7 at follow-up; for Aim 2, recurrent strokes confirmed by neuroimaging; and for Aim 3, the Apgar scores of newborns and results from Ages & Stages Questionnaires, Third Edition (ASQ-3) at follow-up.

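### The ASQ-3 primary outcome for Aim 3 has a stated upper age of 66 months, but roughly a third to a half of the offspring will be older than that at the first follow-up round

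*Protocol article*

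**What the plan says.** The Primary outcome section sets, "for Aim 3, the Apgar scores of newborns and results from Ages & Stages Questionnaires, Third Edition (ASQ-3) at follow-up". Table 3 lists ASQ-3 developmental status among the long-term offspring outcomes, also at follow-up. The Assessment process section gives the instrument's range: "screening comprehensive developmental status in children aged 1 to 66 months".

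The inclusion window is in the section on participating centers and patient population: "ASPP patients and non-ASPP participants from January 2015 to November 2024 will be included". Cases there are "those who experience acute stroke events during pregnancy or within 6 weeks postpartum", so a birth can fall from about 6 weeks before the index stroke to about 9 months after it.

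The Follow-up schedule fixes three rounds: "First follow-up: Conducted between December 2024 and February 2025"; "Second follow-up: Conducted between December 2027 and February 2028"; "Third follow-up: Conducted between December 2030 and February 2031". The content listed for each round concerns the women. No round is named for the offspring assessment.

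Table 1 sets no limit on the child's age or birth year. Pregnant and postpartum controls are matched on maternal age and hypertension history, not on delivery date. The Statistical analysis section plans linear or generalized linear models for ASQ-3 without an age restriction, and its imputation covers baseline data only. Table 2 does list the child's birth date among the variables collected.

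**The concern.** The article itself fixes three design elements: the instrument, the inclusion window and the date of first contact. They do not fit together. A child born in January 2015 is about 10 years old at round 1, and the tool's stated upper limit is five and a half years.

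If the plan is followed as written, one of two things happens. Either a primary outcome is scored in children outside the tool's own stated range, or those children drop out of the primary analysis without the plan saying so. In the second case the denominator is well below the 400 index cases that a reader would assume.

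Whether a child is in range depends only on birth date and interview date. Because controls are not matched on birth date, the in-range share and the ages at assessment can also differ between ASPP offspring and control offspring.

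**Working it through.** The article gives no figure for the share of children in range, so there is nothing to reproduce. The check is calendar arithmetic.

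**Inputs from the article**
- ASQ-3 range: 1 to 66 months (Assessment process).
- Window: January 2015 to November 2024, which is 119 months (Participating centers and patient population).
- Rounds: December to February of 2024-25, 2027-28 and 2030-31 (Follow-up schedule).
- Target of 400 ASPP cases and 20% attrition (Sample size estimates).

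**Assumptions, not in the article**
- Index events are uniform over the window.
- Birth is at the index date (lag 0).
- There is one child per pregnancy.
- Both are varied below: the lag, and the trend in case volume.

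**Cut-off birth date** = interview date minus 66 months. For round 1 this runs from 1 June 2019 (interview 1 December 2024) to late August 2019 (interview end of February 2025).

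**Share over age** = (months from 1 January 2015 to the cut-off, minus the lag) / 119, capped at 100%.

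At mid-round:

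| Round | Cut-off, months after 1 Jan 2015 | Over 66 months |
|---|---|---|
| 1 (mid-January 2025) | 54.46 | 54.46/119 = 45.8% |
| 2 (mid-January 2028) | 90.46 | 90.46/119 = 76.0% |
| 3 (mid-January 2031) | 126.46 | above 119, so 100% |

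**Sensitivity at round 1**
- Interview date, start to end of the round: 53.0/119 = 44.5% to 55.9/119 = 47.0%.
- Birth 3, 6 or 9 months after the index event: 51.46/119 = 43.2%, 48.46/119 = 40.7%, 45.46/119 = 38.2%. Stroke 6 weeks after birth: 55.96/119 = 47.0%.
- Linear trend in case volume with last-to-first ratio r. With u = cut-off/119, the share is [u + (r − 1)u²/2] / [1 + (r − 1)/2]. At u = 0.458 this gives 54.0% for r = 0.5, 37.5% for r = 2 and 33.4% for r = 3.
- r = 3 with a 3-month lag (u = 51.46/119 = 0.432): 31.0%.

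The round 1 range over these variants is about 31% to 54%.

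**If ASQ-3 were repeated.** Round 2 is 76.0% in the base case, 63.8% with tripling volume and a 3-month lag, and 82.1% with halving volume. Round 3 is 100% for lags up to 6 months. With a 9-month lag it is 97.5% (116/119) at the start of the round and 99.9% at the end.

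**Evaluable number at round 1.** After attrition, 400 × 0.80 = 320 per group.
- Base case: 320 × (1 − 0.458) = 173.
- 31% over age: 320 × 0.69 = 221.
- 54% over age: 320 × 0.46 = 147.

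The result is about 150 to 220 per group, before pregnancy losses and terminations. It assumes that control births have a similar calendar distribution, which the matching does not guarantee.

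**The case against.** Several points on the other side have force.

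- **Later rounds.** A reader might infer that ASQ-3 is scheduled at all three rounds and so fails for three quarters of children at round 2 and nearly all at round 3. The article does not say so. It says only that ASQ-3 is measured at follow-up. The figures for rounds 2 and 3 are therefore conditional. What stands is that the round is unspecified and that round 1 already conflicts with the age range.
- **The 46%.** This is not a protocol figure. It rests on uniform births. Births that follow the stroke lower it, and so would growth in case numbers; the Background says incidence appears to be rising. Only the wider range of 31% to 54% should be relied on.
- **Ceiling effects and power.** A reader might go on to say that over-age children would score at the ceiling and mask a deficit, or that a specific amount of power is lost. The documents support neither. They say nothing about scores above 66 months. They give no ASQ-3 event rates and no Aim 3 sample-size calculation against which a loss could be measured.
- **Level of detail.** Stating the tool's range may imply use within it, and an article may leave administration rules to the full protocol. That would explain a missing eligibility sentence. It does not reconcile the three fixed design elements, nor does it tell the reader that a large share of the offspring cannot contribute to this outcome.

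Table 3 also counts health status within a year of discharge as long-term. This does not rescue the older births, because ASQ-3 is set at follow-up and the first contact described is in December 2024.

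**Conclusion.** The point holds for round 1. By the article's own dates and its own description of the instrument, children born before about June to August 2019 are over age for an Aim 3 primary outcome at the first contact. The size is roughly a third to a half of the offspring: 45.8% with uniform births, and 31% to 54% over the trends and lags tried. The existence of the conflict needs no assumption; only its size does.

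For later rounds the conclusion is conditional. If ASQ-3 were repeated, about three quarters would be over age at round 2 and nearly all at round 3. The documents do not support a claim about the direction of bias from scoring over-age children, or a claim about lost power. The other Aim 3 primary outcome, Apgar, is untouched.

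**What to change.** 1. Define the ASQ-3 primary analysis as children aged 1 to 66 months on the interview date, worked out from the birth date already collected. Do not score ASQ-3 in children above 66 months.
2. Name the round or rounds at which ASQ-3 is primary. Round 3 cannot be one. If round 2 is included, say that only about a quarter of the children are expected to be in range.
3. Adjust the ASQ-3 models for age at assessment or birth date, because controls are not matched on it. Matching on birth date would be a design change and is not needed for this purpose.
4. State the expected evaluable number with its assumption: about 150 to 220 per group after 20% attrition, before pregnancy losses and terminations.

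The cost is an amendment to the outcome definition and a smaller stated denominator for this outcome. No new variable is needed. The round 1 interview window closed before the article was published in June 2025, but the restriction and the adjustment can still be applied to data collected then.

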**• Medication history**
▪ Antihypertensive (if with record the duration of antihypertensive medication use, including pre-pregnancy and during pregnancy, and the types of medications, such as methyldopa, labetalol, amlodipine)
▪ Antiplatelet
▪ Oral contraceptive
• **Stroke evaluation**
▪ Type: Ischemic (thrombotic, embolic) or hemorrhagic (intracerebral, subarachnoid)
▪ Etiology
(1) Ischemic stroke (carotid stenosis, intracranial atherosclerotic stenosis, cardiogenic embolic stroke, arterial dissection, pregnancy-related hypercoagulable state, moyamoya disease)
(2) Hemorrhagic stroke (AVM, IA, pregnancy-related hypercoagulable state)
(3) Other stroke types: Cerebral venous thrombosis, cerebral sinus thrombosis, stroke caused by systemic inflammation, hematological disorders (such as thalassemia, aplastic anemia), arterial dissection (such as carotid dissection), cardiovascular diseases (such as valvular heart disease, embolism due to atrial fibrillation)
▪ Location and size: Anterior or posterior circulation, cortical or subcortical
▪ Diagnostic neuroimaging: CT, CTA, MRI, MRA, DSA, etc.
▪ Cardiac examination: ECG, echocardiography, etc.
• **Pregnancy-/puerperium-associated variables**
▪ Week of gestation and trimester at stroke onset^a^
▪ Gestational hypertension
▪ Preeclampsia/eclampsia
▪ HELLP syndrome
▪ Gestational diabetes
▪ Frequency of previous pregnancy and pregnancy-/puerperium-associated stroke
• **Data on delivery**
▪ Type: Spontaneous vaginal delivery, cesarean section, or prenatal termination (induced abortion or labor)
▪ Week of gestation at delivery
• **Stroke management**
▪ Ischemic stroke
(1) Nonsurgical treatment (if with record dose and duration): anticoagulant (heparin, warfarin), antiplatelet (aspirin, clopidogrel), intravenous thrombolysis (alteplase, tenecteplase), etc.
(2) Surgical treatment: mechanical thrombectomy, etc.
▪ Hemorrhagic stroke
(1) Nonsurgical treatment: Supportive (blood pressure control, intracerebral pressure control), etc.
(2) Surgical treatment: Open surgery (clipping for IA, excision for AVM, hematoma evacuation), endovascular intervention (coiling for IA, embolization for AVM), ventriculopuncture drainage, etc.
▪ Time relationship with terminating the pregnancy (if with surgical treatment): after, before, or during the same period
• **Complications**

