▪ Neurologic: Intracerebral rebleeding (hemorrhagic stroke), vasospasm or delayed cerebral ischemia, intracerebral hemorrhage (ischemic stroke), brain herniation, etc.
▪ Systemic: Chest infection, urinary tract infection, deep venous thrombosis, pulmonary embolism, gastrointestinal bleeding, myocardial ischemia, etc.
• **Offspring-related variables**
▪ Term at birth: Pre-term, full-term, or post-term
▪ Gender
▪ Birth date
▪ Birth weight
▪ Apgar scores at 1, 5, and 10 min
▪ Transfer to NICU (if with record etiology)

*BMI* body-mass index, *NIHSS* National Institute of Health stroke scale, *mRS* modified Rankin Scale, *RBC* red blood cell, *WBC* white blood cell, *PLT* platelet, *TC* total cholesterol, *HDL-C* high-density lipoprotein cholesterol, *TT* thrombin time, *PT* prothrombin time, *FIB* fibrinogen, *APTT* activated partial thromboplastin time, *SBP* systolic blood pressure, *DBP* diastolic blood pressure, *AVM* arteriovenous malformation, *IA* intracerebral aneurysm, *CT* computed tomography, *CTA* computed tomography angiography, *MRI* magnetic resonance imaging, *MRA* magnetic resonance angiography, *DSA* digital subtraction angiography, *ECG* electrocardiography, *NICU* neonatal intensive care unit

^a^The first trimester is defined as the period from conception to 12 + 0 weeks of gestation. The second trimester spans from 12 + 1 weeks to 28 + 0 weeks of gestation. The third trimester begins after 28 + 1 weeks of gestation. Puerperium is defined as the period within 6 weeks postpartum

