#### Secondary outcome

These are the following: For Aim 1, unfavorable functional outcomes at discharge; for Aim 2, strokes occurring during subsequent pregnancies; and for Aim 3, the occurrence of intrauterine death, stillbirth, or critical illnesses requiring hospitalization in the offspring (see Table 3).

**Table 3 Tab3:** Outcome measures^a^

• **Women**

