### Statistical analysis

Descriptive statistics will express continuous variables as means (±standard deviation) or medians (interquartile range) and categorical variables as proportions. Chi-square tests or Fisher’s exact tests, along with Student’s *t*-tests or Wilcoxon rank-sum tests, will be used to compare demographics and clinical characteristics between cases and controls. Chi-square tests will compare dichotomous outcomes, while *t*-tests or Mann-Whitney *U*-tests will compare quantitative outcomes. Kaplan-Meier curves and log-rank tests will evaluate survival analyses, with Cox proportional hazard models calculating hazard ratios and 95% confidence intervals (CIs). Multivariate logistic regression will identify independent predictors, and linear or generalized linear models will assess the impact of ASPP and other factors on delivery outcomes and the ASQ-3 results. First, logistic regression will calculate odds ratios and 95% CIs for recurrent stroke. Subgroup analysis will evaluate potential differences in endpoints for predefined subgroups (such as gestational hypertension, preeclampsia, HELLP syndrome, gestational diabetes, trimester, and type of delivery). Multiple imputation will address missing baseline data, with a *p*-value of < 0.05 considered statistically significant.

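### Aim 3 names no offspring outcome for induced termination or for death after live birth, so the ASQ-3 and Apgar comparisons may understate harm if these losses are more frequent after antepartum stroke

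*Protocol article*

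**What the plan says.** The primary outcomes for Aim 3 are "the Apgar scores of newborns and results from Ages & Stages Questionnaires, Third Edition (ASQ-3) at follow-up" (Primary outcome). The secondary outcomes are "the occurrence of intrauterine death, stillbirth, or critical illnesses requiring hospitalization in the offspring" (Secondary outcome). Table 3 repeats this list under Offspring.

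The definitions are given in the text:

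- **Fetal loss** (Assessment process): "Intrauterine death or stillbirth is defined as a dead fetus in the uterus at any trimester or the birth of a dead infant", where the birth limb applies after 28 + 1 weeks. Induced termination is not mentioned.
- **Critical illness** (Table 3 footnote e): "Critical illness is defined as the offspring requiring hospitalization due to a diagnosed disease".
- **Termination** appears in Table 2 under Data on delivery, as one delivery type: "Type: Spontaneous vaginal delivery, cesarean section, or prenatal termination (induced abortion or labor".
- **Mortality** is in Table 3 under the women's long-term outcomes. The offspring lists have no such line.
- **Offspring-related variables** in Table 2 are term, gender, birth date, birth weight, "Apgar scores at 1, 5, and 10 min" and NICU transfer. Vital status is not among them.

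For the analysis, "linear or generalized linear models will assess the impact of ASPP and other factors on delivery outcomes and the ASQ-3 results" (Statistical analysis). Delivery outcomes are not defined. The only stated missing-data rule is multiple imputation of baseline data.

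**The concern.** Two kinds of loss have no named place in the Aim 3 outcomes. A pregnancy that is terminated after the stroke yields no Apgar score and no ASQ-3, and termination is not listed as an offspring outcome. A live-born child who dies before the follow-up call has no ASQ-3, and the death is not counted as a death.

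The Background argues that maternal stroke disturbs fetal blood flow and can lead to fetal distress and asphyxia. On that reasoning the exposure may affect whether a child is born alive and survives to be assessed. A comparison restricted to assessed children then conditions on a possible consequence of the exposure. The Discussion says the results should help physicians inform parents about their children's development. A reassuring result among survivors, with no loss rates beside it, could mislead.

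**Working it through.** The protocol states no sample size, power or event rate for Aim 3, so there is no figure of its own to reproduce. The check has two parts.

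**1. Which outcome catches which event**

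| Event | Apgar | ASQ-3 | Fetal-loss outcome | Critical illness |
|---|---|---|---|---|
| Intrauterine death, or stillbirth after 28 + 1 weeks | no | no | yes | no |
| Termination of a living pregnancy before 28 + 1 weeks | no | no | not named | no |
| Live birth, admitted with a diagnosed disease, then dies | possible | no, if dead before the call | no | yes, as an admission |
| Live birth, dies without such an admission | possible | no, if dead before the call | no | no |

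A later termination by induced labor that yields a dead infant could be read into the birth limb of the fetal-loss definition. The text does not say whether it should be.

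**2. How far a survivors-only ASQ-3 comparison could depart from one that counts losses**

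Inputs:

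- Group sizes from the Abstract: 400 ASPP patients and 400 pregnant or puerperal participants without stroke.
- L, the share terminated or dead, and q, the share with poor ASQ-3 among survivors. Neither is in the protocol, so all values below are assumed. One child per pregnancy is also assumed.

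Formula: risk with losses counted as poor = L + (1 − L) × q.

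With q = 15% (ASPP) vs 10% (controls), the survivors-only risk ratio is 0.15/0.10 = 1.50 in every row:

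| L, ASPP vs control | Pregnancies lost out of 400 | ASPP risk | Control risk | Risk ratio |
|---|---|---|---|---|
| 2% vs 2% | 8 vs 8 | 0.02 + 0.98 × 0.15 = 0.167 | 0.02 + 0.98 × 0.10 = 0.118 | 1.42 |
| 5% vs 1% | 20 vs 4 | 0.05 + 0.95 × 0.15 = 0.1925 | 0.01 + 0.99 × 0.10 = 0.109 | 1.77 |
| 10% vs 1% | 40 vs 4 | 0.10 + 0.90 × 0.15 = 0.235 | 0.109 | 2.16 |
| 20% vs 2% | 80 vs 8 | 0.20 + 0.80 × 0.15 = 0.32 | 0.118 | 2.71 |

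With q = 10% in both groups, the survivors-only ratio is 1.00. Counting losses gives 0.145/0.109 = 1.33 (5% vs 1%) up to 0.28/0.118 = 2.37 (20% vs 2%).

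**When the direction holds.** Rearranging the formula, the ratio with losses counted exceeds the survivors-only ratio only if the ratio of losses (ASPP to control) exceeds the odds ratio for poor ASQ-3 among survivors. For 15% vs 10% that is (0.15 × 0.90)/(0.10 × 0.85) = 1.59. If survivors do not differ, any excess of losses is enough.

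The illustration shows only the effect of leaving losses uncounted. It does not model whether the surviving ASPP children are a healthier selection.

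**The case against.** Three stronger readings are tempting, and the protocol does not support them.

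- **That children who die after live birth drop out of Apgar as well.** Apgar is scored within 10 minutes of birth, so they can have scores and count for asphyxia. Those admitted with a diagnosed disease also count as critical illness. Only ASQ-3 depends on survival to the call.
- **That the worst results vanish from Aim 3.** Intrauterine death at any trimester and stillbirth are already secondary outcomes.
- **That the estimated harm is too small, as a fact.** This needs sufficiently more loss after stroke than in controls, and the protocol gives no rates. With equal losses the survivors-only ratio is the larger one (1.50 against 1.42). After a postpartum stroke, birth and Apgar come before the stroke and no termination of that pregnancy can follow. Some terminations may also be elective or made for the mother's treatment, so they are not evidence that the remaining offspring are healthier. A calculation within the ASPP group alone would show only that adding a component raises the rate, not that the comparison is biased.

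It can also be said that termination is visible in the data: type of delivery is recorded, delivery data are collected for non-ASPP participants, type of delivery is a predefined subgroup, and delivery outcomes are modelled. That is true, but none of it makes termination an offspring outcome, and delivery outcomes are undefined.

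Finally, handling of ASQ-3 after death may be left to an analysis plan. That is fair for the method. It does not cover the outcome list, which the article fixes in detail. Child death is neither a listed outcome nor a listed variable, and an analysis plan cannot recover what was not asked.

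**Conclusion.** The point holds in a conditional form. The Aim 3 outcomes have no named place for induced termination or for death after live birth, so ASQ-3 is compared among surviving children and Apgar among live births. If such losses are clearly more frequent after antepartum stroke than in pregnant controls, these comparisons may understate harm to offspring. On the assumed rates, a ratio of 1.50 among survivors stands against 1.77 to 2.71 with losses counted, and a null result among survivors against 1.33 to 2.37. These figures rest wholly on assumed loss and ASQ-3 rates and on counting every loss as a poor result. They show possible size, not expected size. The excess is plausible on the protocol's own mechanism but is not shown. The gap is worth closing because it determines what Aim 3 can conclude and the repair is cheap.

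**What to change.** 1. Add two offspring outcomes to Table 3: neonatal or child death (with date), and pregnancy termination (with the reason where recorded). State whether a late induced labor with a dead infant counts as termination or as stillbirth.
2. Report both, together with intrauterine death and stillbirth, as proportions of all pregnancies in the ASPP group and the pregnant non-stroke group, beside the Apgar and ASQ-3 results. Show antepartum strokes separately. Controls have no index event and are matched on age and hypertension history, not gestational age. For this comparison, restrict them to pregnancies at a gestational age comparable with the case's at stroke onset.
3. Label Apgar as conditional on live birth and ASQ-3 as conditional on survival.
4. Add a sensitivity analysis that counts death as a poor developmental result, with and without terminations. The poor ASQ-3 category must be defined for this.

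Cost: wording in Table 3, one telephone question and one further analysis. The first follow-up window (December 2024 to February 2025) closed before the article appeared. If the question was not asked then, it can go into the 2027–28 round and be answered retrospectively. Delivery type is already collected. The reason for termination is not a listed variable, so it must be collected from records or left as unknown. An ordered outcome with loss as the worst category is possible but debatable, and is not needed here.
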